We will conduct a 10-week, multi-method, randomized study, and will recruit 200 school-based adolescents, ages 12-18 years, with daily or near daily cannabis use and current depressive symptoms. The study design is nearly identical to that used in another IRB approved protocol aimed at pilot data collection for the current protocol (#2021P002416), apart from minor modifications to the study population. Participants will complete 2 weeks of real-time EMA during baseline cannabis use (EMA Phase 1; Baseline Use as Usual) to quantify the temporal relationship between cannabis use and mood and SI, and the within- (e.g., concurrent other substance use, social context of use) and between-subject factors (e.g., average severity of cannabis use, depression and SI) that may moderate these linkages. To determine how depression and SI change across short- and longer-term cannabis withdrawal, participants will then be randomized to 8 weeks of monitoring (CB-Mon) or incentivized abstinence via contingency management (CB-Abst). A key aspect of the approach is that the 8-week period is long enough to observe true changes due to cannabis discontinuation, separate from effects of withdrawal and residual cannabinoid exposure that generally subside in 4 weeks. Both groups will complete 1 week of EMA in weeks 1 (EMA Phase 2; Randomized Withdrawal) and 8 (EMA Phase 3; Randomized Sustained Abstinence) of the randomized study period. During all 3 EMA phases, participants will receive 7-9 random, time-stamped prompts per day to ascertain mood and SI in the absence of acute cannabis use, proximal but prior to cannabis use, and during or shortly after cannabis use.

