**Inclusion Criteria**

1. Ages 12-18;
2. Current daily or near daily cannabis use (i.e., use ≥ 4 days per week on average; Timeline Followback);
3. Score ≥ 5 on PHQ-9;
4. Access to an internet-capable smartphone (iOS or Android);
5. Provision of at least 1 collateral contact for risk monitoring;
6. Provision of informed assent (or consent if 18 years) and parent/guardian consent if <age 18;
7. Approximately 50% response rate to EMA prompts during the first EMA phase (Baseline as Usual);
8. No immediate plan to discontinue cannabis use in the next 3 months;
9. Positive toxicology result for cannabis on baseline urinalysis.

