**Local Recruitment Procedures**

All recruitment procedures are identical to those used in IRB approved pilot protocol #2021P002416. Participants will be adolescents between the ages of 12-18 years and referred to the study via: 1) annual on-campus or virtual screenings as part of a separate IRB-approved screening protocol (#2021P001873), 2) through an IRB-approved universal phone screening protocol (#2024P002895) designed to systematically assess eligibility for multiple IRB-approved studies at once, and 3) on a case by case basis through direct physician, teacher, administrator referrals and parent or participant request. Participants will be referred through the community via postings online, flyers, and through social media advertisements (Twitter, Reddit, Snapchat). We will also work with a recruiting platform, BuildClinical, to advertise on social media platforms. All advertisements will be IRB approved. Potential participants will complete a telephone screen for eligibility. We are will use OutFront, an MGB-approved vendor, to expand our study outreach for recruitment. Study flyers will appear across a network of MBTA trains and busses that link to the study MGB Rally page. In addition, participants will be recruited using the Research Patient Data Registry (RPDR) through MGB, a clinical data registry that can identify patients for clinical trials. We will run queries on RPDR to find subjects with current depression, current suicidal ideation, and current cannabis use reported for at least >4 days per week, therefore likely to meet our eligibility criteria for this research study. Subjects identified through these mechanisms and who have not opted out of receiving research invitations will receive a personalized letter through their patient gateway account detailing parts of the study and contact information for our study staff, should they be interested in learning more. For those subjects who are under the age of 18, research initiations will be sent to parents/legal guardians that have not opted out of receiving such letters.

1. **Subject Enrollment**

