**Assessment Techniques**

Participants will complete 12 study visits across ~10 weeks and three waves of EMA data collection. To minimize burden and maximize feasibility, study visits will be conducted in a private room at a participant’s school campus or local library, in lab settings, or virtually via video conferencing (via MGB-approved video conference platforms like Microsoft Teams or zoom). Visits will entail collection of urine samples for verification of self-reported use and abstinence verification (for CB-Abst post-randomization), as well as brief questionnaires and interviews on interim substance use, craving, and withdrawal. Questionnaires and surveys on mood symptoms and suicidal ideation (SI) will be conducted by study staff blinded to group assignment.

**Semi-Structured Interviews:** Substance use disorders and other psychiatric diagnoses will be queried at the baseline with past and current modules of the Mini International Neuropsychiatric Interview (MINI) Kid 7.0.2, which was designed as a brief structured diagnostic interview for the major psychiatric disorders across development in DSM-5 (Sheehan, Sheehan, & Shytle et al., 2010). We will evaluate for cannabis use disorder, major depressive disorder, as well as other Axis I diagnoses (including those specific to developmental populations). At the baseline visit, we will administer the Self-Injurious Thoughts and Behaviors Interview (Nock et al., 2007) to assess lifetime self-injurious thoughts and behaviors and confirm past month SI. We will also conduct the Columbia-Suicide Severity Rating Scale (Posner et al., 2011) at V1 to capture in-depth information about past month SI. At V2-12, SI and behavior since last visit will be determined with the Columbia-Suicide Severity Rating Scale *(alongside the primary corresponding EMA measure).* Interviews will be administered by trained study staff with established interrater reliability.

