**Potential Benefits to Society**

Information developed from this study may help researchers in the future. The expected scientific yield of the project is substantial. There is much to be learned from the project. Findings have the potential to have measurable implications on policy, prevention, and treatment efforts. The greatest benefit will be to future cohorts of adolescents who will benefit from what is learned from this research project.

The risks associated with this study are minimal and reasonable, particularly in light of the fact that significant knowledge will be gained.

1. **Statistical Analysis**

**Data preparation.** Six negative affect measures will be defined via composite averages and individual scores using EMA items: 1) the average over 5 items assessing depleted mood (scores for feeling Sad, Self-hatred, Numb, Hopeless, and Fatigued), 2) the average over 2 items assessing negative cognitive impacts (scores for feeling Disinterested and Inattentive), 3) the average over 3 items assessing negative activation (scores for feeling Agitated, Irritated, and Anxious), 4) the average over 3 items assessing passive suicidal ideation (scores for Thoughts about death, Wishing suffering could be over, and Better off as dead), 5) the individual item for suicidal urges, and 6) the individual item for non-suicidal self-injury urges. All items will be measured on a 0 (No, not at all) – 100 (Yes, very much) scale. Acute cannabis use will be defined as a binary indicator variable (1 = self-reported use in the hour preceding the current random prompt, 0 = no use in the last hour).Additionally, whether cannabis was used in the last hour to improve negative mood will be assessed on a 0 (No cannabis use) and 1 (No, not at all) – 100 (Yes, very much) scale.

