**Statistical models.** Separate analyses will be conducted for each negative affect measure. Statistical models will assume that a) data are a mixture of a non-zero continuous component and zeros, and b) the continuous component will follow a beta distribution (i.e., scores will be scaled to be between 0 and 1). Models will include 1) a participant-varying lag-1 autocorrelation term (to handle repeated measures) and 2) a participant-varying probability term governing the occurrence of zeros (to allow for individual differences). Additional covariates will include weekday (categorical, Monday-Sunday), time of day (categorical, 6:00-11:00, 11:00-16:00, 16:00-21:00), age (continuous), and gender (categorical). To test specific hypotheses, additional predictors will be included as needed for a) the beta regression, b) the residual variance term of the beta regression, and c) the probability term governing zeros.

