**Protocol non-adherence.** Analyses involving phase 1 and/or phase 2 of EMA data collection, will only consider CB-Abst participants who have biochemically-validated CB abstinence for two months because the goal is to study the effect of abstinence on change in mood and SI. If fewer than expected CB-Abst abstain from CB use for the full two months, we will form Helmert contrasts: those in CB-Mon (a), CB-Abst who do not abstain (b), and CB-Abst who abstain (c). The 1^st^ Helmert contrast will compare a to b+c and will be the intent to treat comparison. The 2^nd^ contrast will compare b to c, which corresponds to the post hoc sensitivity analysis of interest. Similar considerations will be made if participants in CB-Mon incidentally discontinue CB use during the study.

**Power analysis and justification of recruitment targets for the confirmatory cohort.** The R package ‘EMAtools’ (version 0.1.3; Kleiman, 2017) was used to determine the power for the proposed analyses. Preliminary analyses from the exploratory study found effect size estimates for significant effects ranged from 0.19 to 0.44, and that 77% of participants completed all phases of the study, completing on average 76% of all prompts. Estimates of the power were therefore computed to detect a weak effect (a Cohen’s d of .2) based on linear multi-level models using the nesting structure for the proposed EMA analyses and an intra-class correlation of .09. Table 1 shows the breakdown of estimates power based on the hypothesis being tested under two scenarios: 1) an ideal scenario with the full proposed number of participants and responses, and 2) a realistic scenario where 77% of participants complete 76% of entries.

Table 1: Power estimates by hypothesis and attrition scenario (ideal versus worse-case)

| Hypothesis | N (%) for sample size | N (%) of completed entries | Power |
| --- | --- | --- | --- |
| 1.1 - 1.2 | 200 (100%) | 112 (100%) | 99% |
|  | 154 (77%) | 85 (76%) | 93% |
| 2.1 - 2.2 | 200 (100%) | 224 (100%) | 99% |
|  | 154 (77%) | 170 (76%) | 94% |

1. **Monitoring and Quality Assurance**

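### Table 1's 93–99% power counts every participant and every completed prompt, so it cannot be claimed for the three suicidal-ideation and self-injury measures, whose mean and variability are tested on non-zero scores only.

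*Protocol*

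**What the plan says.** **Who enters.** The only symptom item in the Inclusion Criteria is "Score ≥ 5 on PHQ-9", and neither the inclusion nor the exclusion list mentions SI. General Description of Study Design likewise describes adolescents "with daily or near daily cannabis use and current depressive symptoms". Two other sections read as if SI were expected. Local Recruitment Procedures queries the patient registry for "current depression, current suicidal ideation, and current cannabis use reported for at least >4 days per week, therefore likely to meet our eligibility criteria". Assessment Techniques has the baseline self-injury interview serve "to assess lifetime self-injurious thoughts and behaviors and confirm past month SI".

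**What is analysed.** Data preparation defines six measures. Three are mood measures: depleted mood, negative cognitive impact and negative activation. The other three are a passive-SI composite and "5) the individual item for suicidal urges, and 6) the individual item for non-suicidal self-injury urges". Hypotheses 1.2, 2.1 and 2.2 all concern the level and variability of SI.

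**How.** Statistical models assumes that "data are a mixture of a non-zero continuous component and zeros", with a beta distribution for the non-zero part and a participant-specific probability of a zero. Data analysis places the Hypothesis 1.2 and Aim 2 predictors in the beta regression and its residual variance.

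**Power.** The calculation uses linear multilevel models, d = 0.2 and ICC 0.09. The power section states: "Table 1 shows the breakdown of estimates power based on the hypothesis being tested under two scenarios". Table 1 gives 99% and 93% for Hypotheses 1.1–1.2 (200 × 112 and 154 × 85 participants × entries) and 99% and 94% for Hypotheses 2.1–2.2 (200 × 224 and 154 × 170).

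**The concern.** Power is calculated for one model and the analysis uses another. The difference matters most where zeros are common. A sample admitted on mild depressive symptoms, with no SI requirement, may contain many participants who rarely or never score above zero on suicidal or self-injury urges. For the mean and variability tests, those zeros are not observations.

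These measures are half of the outcome set, and SI is a headline of both aims. A null result on suicidal urges would be read as coming from a test with more than 90% power, and the plan gives no basis for that reading.

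**Working it through.** **1. Do all-zero series inform the beta tests?** Under the stated model a zero contributes only the log of the zero probability. For 112 zeros with zero probability 0.97, the log-likelihood is 112 × ln(0.97) = −3.41. It stays −3.41 at beta means of 0.1, 0.3 and 0.6 and at precisions of 2 and 10. Such a series carries no information on the beta mean or residual variance. The same holds for each single zero prompt from other participants.

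**2. Reproduce Table 1.** Take d = 0.2 and ICC = 0.09 as stated, and assume two-sided 0.05, which is not stated. Let D = 1 + (m − 1) × 0.09, n_eff = N × m / D, z = 0.2 × √(n_eff/4), power = Φ(z − 1.96).

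| N × m | D | n_eff | z | Power | Stated |
|---|---|---|---|---|---|
| 200 × 112 | 10.99 | 2,038 | 4.51 | 99.5% | 99% |
| 154 × 85 | 8.56 | 1,529 | 3.91 | 97.4% | 93% |
| 200 × 224 | 21.07 | 2,126 | 4.61 | 99.6% | 99% |
| 154 × 170 | 16.21 | 1,615 | 4.02 | 98.0% | 94% |

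The ideal rows reproduce. The realistic rows come out higher than stated; they match (92.9% and 94.1%) if the 77% is applied twice (154 × 0.77 ≈ 119). That is an inference, it is conservative, and it is a separate matter.

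**3. Same method, with a share f of participants informative.** The protocol gives no f, so 25–75% is an assumed range.

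| f | H1 ideal | H1 realistic | H2 ideal | H2 realistic |
|---|---|---|---|---|
| 75% | 97.4% | 92.3% | 97.9% | 93.6% |
| 50% | 89.1% | 79.0% | 90.3% | 81.1% |
| 25% | 61.7% | 49.8% | 63.5% | 52.0% |

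With the 77% applied twice, the realistic columns become 84/86%, 68/70% and 40/42%. On this method, 80% power needs about 37–39% of participants informative in the ideal rows and 49–52% in the realistic rows.

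**4. Within-person contrasts.** Hypothesis 1.2 compares prompts within a person, and Hypotheses 2.1–2.2 compare phases within a person. The participant intercept cancels, leaving residual variance 1 − 0.09 = 0.91. Take the realistic scenario with f = 25%.

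- *Hypothesis 1.2.* There are M = 0.25 × 154 × 85 = 3,272.5 prompts. Let p be the share of prompts after use, assumed 10–20%. Then SE² = 0.91 × [1/(Mp) + 1/(M(1 − p))]. At p = 10%, SE = 0.0556, z = 3.60 and power is 94.9%. At p = 20% it is 99.8%.
- *Phase 2 vs phase 1 in the abstinence arm.* There are 0.25 × 77 = 19.25 participants with 85 and 42.5 prompts. SE² = 0.91 × [1/1,636 + 1/818] = 0.00167, z = 4.90, power 99.8%.
- *Group-by-phase interaction.* The variance doubles, z = 3.46, power 93.3%.

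Now let only part of those participants' prompts be non-zero:

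| Non-zero prompts | H1.2 | Phase contrast | Interaction |
|---|---|---|---|
| all | 95–99.8% | 99.8% | 93% |
| half | 72–92% | 93% | 69% |
| a quarter | 44–67% | 69% | 41% |

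These figures ignore autocorrelation and between-person variation in the effect, both of which would normally lower them. They also take 77 per arm, before the restriction to confirmed abstainers.

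**The case against.** The strongest reply has four parts.

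- **No SI at entry is not zero throughout.** The passive-SI composite is above zero if any one of its three items is, including wishing suffering could be over. Self-injury urges are not fixed by SI status at entry, and SI may emerge in withdrawal, as Hypothesis 2.1 predicts. This stands. A reader might infer that everyone without SI at entry is lost to these tests; the protocol does not support that.
- **Zeros are not wasted.** Statistical models allows hypothesis predictors in the zero probability as needed, so a participant who moves from zero to non-zero is informative there. This also stands, but it does not rescue the power stated for the mean and variability tests.
- **The design-effect formula suits comparisons between people.** For within-person contrasts it overstates the loss, as step 4 shows. The pilot used the same eligibility criteria apart from the upper age limit, so d = 0.2 may already carry dilution from zeros. Cutting N as well could then count it twice. Both points stand against printing any single corrected figure.
- **The eligibility wording is minor.** The registry query is one recruitment route and may simply be an enriched search. That is fair, although having an interview confirm past-month SI does presuppose it.

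Outcome-specific power might be left to an analysis plan. But the protocol itself publishes one figure as the justification of its recruitment targets, for hypotheses that name SI.

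**Conclusion.** The point holds in a limited form. Table 1's 93–99% cannot be claimed for the mean and variability tests of passive SI, suicidal urges and self-injury urges, because the planned model does not use zero scores for those tests and eligibility does not require SI. It bears on Hypotheses 1.2, 2.1 and 2.2. In Hypothesis 1.1 the affect measures are predictors, so that test is affected differently.

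The size cannot be fixed from the protocol. It depends on the share of participants with any non-zero score, the share of their prompts that are non-zero, and how far effects vary between people. Across the assumed ranges, power runs from little changed to about 40%. A reader might infer that true SI power is 50–80%. That range follows only from a between-person formula with an assumed share, and the documents do not support it as the corrected value.

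One further dependency: the MetricWire text gives a 1–100 scale for these items and Data preparation gives 0–100. On a 1–100 scale the lowest answer is not a zero, so the zero component is undefined until the two are reconciled.

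**What to change.** 1. State that the current Table 1 rows apply to depleted mood, negative cognitive impact and negative activation.
2. Add rows for passive SI, suicidal urges and self-injury urges. Compute them under the planned zero-inflated beta model and the actual within-person and group-by-phase contrasts, using the pilot's participant-level and prompt-level non-zero rates. Do not print 50–80% as the corrected value.
3. State that beta-part results for these measures describe non-zero reports, and report the zero-part effect beside them.
4. Reconcile the SI wording in Local Recruitment Procedures and Assessment Techniques with the Inclusion Criteria, and the 1–100 scale with the 0–100 scale.

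The cost is some protocol wording, one simulation from pilot data and one added block in Table 1. Enrolment does not change. The stated power for SI will probably look less favourable.

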**Data analysis.**

**Aim 1: To test if negative mood and SI are temporarily relieved and stabilized through acute cannabis use (i.e., negative reinforcement cycle).** We will only use phase 1 data, the 2-week baseline period in which all participants may use cannabis. *Hypothesis 1.1:* We hypothesize that negative affect measures for a) the current random prompt, and b) the prior random prompt (a lag-1 term) will predict 1) greater cannabis use independent of motivating reason (i.e., lower probability for the zero component of the model), and 2) higher scores for motivated cannabis use to improve negative mood. Negative affect measures will therefore be converted to z-scores for this analysis and included as predictors for both the zero and non-zero components of the model. *Hypothesis 1.2:* We hypothesize that the binary indicator for cannabis use in the last hour will predict lower, less variable scores for the negative affect measures. Therefore, the binary use indicator will be included as a predictor for the beta regression residual variance term as well. *Hypothesis 1.3 (exploratory):* There will be within-subject correlates (e.g., concurrent other substance use, social context of use) and between-subject factors (e.g., cannabis use and depression severity, history of suicidal behavior) that moderate relationships between acute cannabis use and negative affect.

**Aim 2: To test if negative mood and SI initially increase with the start of abstinence and then decrease in both mean levels and variability after cannabis wash-out.** We will use phase 1 – 3 data, including predictors for a) group differences (CB-Abst vs. CB-Mon), b) differences by phase (phase 3 vs. phase 1 and phase 2 vs. phase 1), and c) terms for the group by phase interactions. All terms will be included as predictors for the beta regression residual variance term as well. We will only include data for the CB-Abst group with confirmed abstinence for phases 2 – 3. *Hypothesis 2.1:* We hypothesize that CB-Abst will show higher mean negative affect scores and greater variability during phase 2 compared to phase 1, while CB-Mon will show no differences between phases. *Hypothesis 2.2:* We hypothesize that CB-Abst will show lower mean negative affect scores and less variability during phase 3 compared to phase 1, while CB-Mon will show no differences between phases.

**Exploratory analyses:** To further assess heterogeneity in suicidal ideation, we will conduct a set of

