
**Multiple testing.** We will use the false recovery rate adjustment to control for multiple testing across the 6 negative affect measures separately for each hypothesis (Benjamini, 1995).

*Sleep & Circadian Rhythms (Exploratory).* Fitbits will be worn throughout the trial to assess changes in sleep. Sleep, circadian, and physical activity exploratory Fitbit metrics include: *Sleep duration*: mean and standard deviation [StD]) over the main sleep period, the day, and 24hrs; short (<6 hrs) and long (>9hrs) mean nocturnal sleep duration; *Sleep fragmentation*: Mean and StD of 7-day sleep efficiency and wake after sleep onset; *Sleep timing placement*: Mean sleep onset, offset, and mid-point; categorized also as advanced (sleep onset <0900) and delayed (sleep onset >0200); *Sleep timing variability:* Across-day StD of sleep onset, inter-and intra-day stability; sleep offset, and sleep mid-point; relative activity- adjusted amplitude;192 *Physical activity:* Overall activity, time spent walking, in moderate and physical activity. Timing of maximal physical activity will be used in analyses of rest-activity rhythm.

**Missing Data***.* Some data will inevitably be missing. We will explore patterns of missingness to determine if missingness is occurring at random (MAR) (i.e., unrelated to the value of the missing observation) or missing not at random (MNAR). For each analysis, we will use a variety of recommended strategies to address the issue of missing data (e.g., multiple imputation, maximum likelihood estimation) (Schafer & Graham, 2002). Consistency in findings across missing data methods will enhance our confidence in the findings. If findings are discrepant, we will assume that participants randomized to CB-Abst have resumed using cannabis, if they are lost to follow-up.

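### Table 1's power for Hypotheses 2.1–2.2 (99% and 94%) is not the power of the Aim 2 analysis that the protocol plans

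*Protocol*

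**What the plan says.** The paragraph on power and recruitment targets (Protocol, Statistical Analysis) names its tool: "The R package ‘EMAtools’ (version 0.1.3; Kleiman, 2017) was used to determine the power for the proposed analyses". Power was "computed to detect a weak effect (a Cohen’s d of .2) based on linear multi-level models". The intra-class correlation is set at .09. Retention of 77%, prompt completion of 76% and the range of effect sizes are credited to the exploratory study. No source is given for the intra-class correlation, and no alpha is stated.

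For Aim 2, Table 1 prints "2.1 - 2.2 | 200 (100%) | 224 (100%) | 99"% for the ideal case and "154 (77%) | 170 (76%) | 94"% for the case described as "a realistic scenario where 77% of participants complete 76% of entries".

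Other parts of the same section define the analysis that these rows should describe:
- **Data analysis, Aim 2:** group, phase and group-by-phase terms are fitted to the mean and to the residual variance. On the analysis set it says "We will only include data for the CB-Abst group with confirmed abstinence for phases" 2 to 3.
- **Protocol non-adherence:** CB-Abst participants count only with two months of biochemically validated abstinence. If fewer abstain than expected, Helmert contrasts are used. The first compares CB-Mon with all of CB-Abst and is labelled intent to treat.
- **Multiple testing:** an adjustment is made to "control for multiple testing across the 6 negative affect measures separately for each hypothesis".
- **Statistical models:** the outcome model combines a zero component with a beta regression.

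**The concern.** Table 1 is the protocol's justification for recruiting 200. For Aim 2 it differs from the planned analysis in four ways.

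1. **Analysis set.** The 77% is a study-completion rate. The planned exclusion of non-abstinent CB-Abst participants comes on top of it, and the 154 is not reduced for it.
2. **Error rate.** The power text does not mention the FDR step over six measures.
3. **Contrast.** The figures behave like a comparison of two overall means. Hypotheses 2.1 and 2.2 concern change between phases by group, and each also claims a change in variability, for which there is no power figure.
4. **Intra-class correlation.** The one planning input that controls the design effect has no stated origin.

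What is at stake is how a null result would be read. Someone relying on 94% in an unfavourable scenario would take a null mood or suicidal ideation (SI) finding as well-powered evidence of no effect, and the table does not establish that.

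**Working it through.** **Inputs from the protocol.** d = 0.2 and ICC = .09. Participants: 200, or 154 = 0.77 × 200. Scheduled prompts: 112 for Aim 1 and 224 for Aim 2. Completed prompts in the realistic case: 85 and 170 (76%). Allocation is 1:1, so 154 completers are taken as 77 per arm. **Assumed:** two-sided alpha of 0.05, because none is stated.

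**Step 1: reproduce Table 1.** Compare two group means on effective sample size:

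N_eff = N × completed prompts / [1 + (k − 1) × ICC], SE = √(4 / N_eff), power = Φ(d/SE − 1.96).

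With k = scheduled prompts, the design effect is 1 + 111 × .09 = 10.99 for Aim 1 and 1 + 223 × .09 = 21.07 for Aim 2.

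| Row | N_eff | d/SE | Power | Printed |
|---|---|---|---|---|
| H1, 200 × 112 | 2038 | 4.52 | 99.5% | 99% |
| H1, 154 × 85 | 1191 | 3.45 | 93.2% | 93% |
| H2, 200 × 224 | 2126 | 4.61 | 99.6% | 99% |
| H2, 154 × 170 | 1243 | 3.53 | 94.1% | 94% |

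All four rows are recovered with every completer counted, no FDR step and no phase contrast. With k = completed prompts, the realistic rows become 97.4% and 98.0%.

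**Step 2: apply the abstinence restriction by the same method.** Keep 77 in CB-Mon and 77q in CB-Abst, where q is the abstinent share of completers. q is assumed, because the protocol gives no rate. Each participant contributes 170 / 21.07 = 8.07 effective observations, so SE = √[(1/77 + 1/(77q)) / 8.07]. The strictest FDR step is 0.05/6 = 0.0083, with critical value 2.638.

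| q (assumed) | SE | Power at 0.05 | Power at 0.05/6 |
|---|---|---|---|
| 100% | 0.0567 | 94% | 81% |
| 60% | 0.0655 | 86% | 66% |
| 40% | 0.0751 | 76% | 51% |

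True power under the FDR rule lies between the two columns.

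**Step 3: the ICC within that method.** With all 154 at alpha 0.05, an assumed ICC of 0.2 gives 67% (k scheduled) to 78% (k completed). An assumed ICC of 0.3 gives 50% to 61%.

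**Step 4: the group-by-phase contrast.** In a linear random-intercept approximation the person intercept cancels. With 85 completed prompts in phase 1 and 42.5 in a one-week phase (half of 85), the variance of one person's change is .91 × (1/85 + 1/42.5) + τ² = 0.0321 + τ². Here τ² is the person-level variance of change with total variance 1, which the protocol does not give. SE = √[(0.0321 + τ²)(1/77 + 1/(77q))]. At q = 40% and alpha 0.05:

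| τ² (assumed) | SE | d/SE | Power |
|---|---|---|---|
| 0 | 0.0382 | 5.23 | 99.9% |
| .05 | 0.0611 | 3.27 | 91% |
| .09 | 0.0745 | 2.68 | 77% |

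The planned contrast can therefore have more or less power than the printed 94%, depending on a quantity the protocol does not state.

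**The case against.** **Is the table miscalculated?** The usual design effect at completed prompts gives 97.4% and 98.0%, so a reader might infer that the realistic rows are wrong or that attrition was taken off twice (154 × 0.77 = 118.6 participants gives 92.9% and 94.1%). The documents do not support this. Using scheduled prompts in the design effect recovers all four rows, so no arithmetic error is shown. On their own inputs the printed realistic values are, if anything, conservative.

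**Is Aim 2 underpowered?** A reader might also infer power well below 80%. The low figures in Steps 2 and 3 use the overall-means comparison, which is not the planned contrast. For the planned contrast a higher intercept ICC does not by itself reduce power, and with no person-level variation in change power is 99.9% even at 40% abstinent. The 0.05/6 column is a worst case, because the FDR thresholds rise if several measures respond.

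**Does the fallback answer the point?** If abstinence is low, the first Helmert contrast keeps all CB-Abst completers. That is fair, but the effect in that set is probably diluted, and Table 1 does not state power for it either.

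**Is this a refinement best left elsewhere?** The linear approximation is openly disclosed, and an unsourced planning ICC is not a contradiction in itself. However, the protocol prints the figures as its justification and labels the scenario realistic while leaving out its own exclusion and error control. That mismatch stands.

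**Conclusion.** The point holds in limited form: the 99% and 94% printed for Hypotheses 2.1–2.2 do not belong to the planned Aim 2 analysis. They count CB-Abst completers whom the plan would exclude, omit the FDR step, describe a different contrast, leave the variability hypotheses without a figure, and rest on an ICC of unstated origin.

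The size is conditional. Under the method that reproduces the table, 94% becomes 86% or 76% when 60% or 40% of CB-Abst completers are abstinent, and 66% or 51% at the strictest FDR step. For the planned contrast at 40% abstinent and alpha 0.05, the range is 99.9% to 77% as the variance of change goes from 0 to .09. The abstinent shares, the two-sided 0.05 and the variances of change are all assumptions, so neither the direction nor the amount of the gap is established.

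The analysed number is also not fixed, because the abstinence rule is worded differently in the Aim 2 text (phases 2 to 3) and under Protocol non-adherence (phase 1 and/or phase 2, for two months).

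**What to change.** Restate the H2.1–2.2 rows of Table 1 as follows:
- Compute power for the group-by-phase contrast.
- Do so for both analysis sets: the abstainer subset at a stated expected abstinence rate, and the all-randomised Helmert (intent-to-treat) contrast with a diluted effect.
- State the alpha and apply the FDR rule over the six measures.
- Take the ICC and the person-level variance of change from the exploratory study, name that source, and show a range for each.
- Give the variability hypotheses their own figure, or state that they are not powered.
- Reconcile the two wordings of the abstinence restriction so that the analysed number is defined.

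The cost is a few hours of simulation from the exploratory data. N does not change. The restated power may turn out lower or higher than 94%.
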